**1.9 Problem statement**

It has been estimated that zinc deficiency affects about one-third of the world’s population, with a prevalence of 4% to 73% across sub regions in Sub Saharan Africa. This degree of inadequacy is shocking when the requirements of iron and zinc are lacking. Growth is impeded, immune function is depressed, hair is lost, and susceptibility to and severity of infections is increased. In addition, neurobehavioral abnormalities occur due to increased number of opiate receptors in the hypothalamus, in parallel with decreased beta-endorphin and increase metenkephalin (Mahan *et al*., 2012). Iron deficiency and iron deficiency anaemia are two of the most common nutritional deficiencies among children in the world (Monárrez-Espino *et al*., 2011; Mahan *et al*., 2012). The WHO estimates that iron deficiency anaemia affects quarter of the world population and is more prevalent in pre-school children, particularly Africa. Furthermore, the deficiency of these micronutrients is caused by consumption of staple foods and cereal crops that have low micronutrient bioavailability (Uchendu, 2011).

*Cucurbita moschata* (butternut) seeds are considered generally to be agro-industrial wastes and are discarded (Patel, 2013; Patela and Raufb, 2017). In many communities around the world, the seeds are consumed raw, roasted or cooked, but only at the domestic scale. In addition, many communities in South Africa use to consume the roasted *Cucurbita moschata* seeds with porridge. Consumption has been associated with poverty. Instead of being used as a food source, these are discarded or preserved for future use. *Cucurbita moschata* contains adequate levels of minerals such as iron, zinc, copper, calcium, potassium and phosphorus (Patel, 2013; Patela and Raufb, 2017). Despite the legislated fortification of staple foods in South Africa since 2003 (SANHANES-1, 2013), there is a general shortage of micronutrients in a large part of the diet of the population. Inadequate micronutrient intake also has been identified among segments of infant’s in South Africa due to improper practices of feeding children.

Food-based approaches encourages the consumption of foods that are naturally rich in micronutrients; this approach favour locally available foods and considers local, culturally acceptance food habits. This approach recognizes the nutritional value of food for good nutrition by encouraging the enjoyment of variety of foods and supporting rural livelihoods (Darnton-Hill and Cogill, 2010). According to Gibson (2011), the approach equips people to consider their total diet in relation to their preferences, individual lifestyle factors, physiological requirements and physical activity. Neumann *et al*. (2011) revealed that food-based strategies are encouraged as safe methods for controlling and preventing micronutrient deficiencies (Kalimbira *et al*., 2010). Success of a food-based programme for the very poor occurs when each member in the household has access to adequate dietary intake that is optimal for maintaining micronutrient status (Arimond *et al*., 2011; Gibson, 2011).

Infections in children is caused by group of parasites commonly known as worms such as hookworms, whipworms and roundworms. These infections are soil transmitted helminth infections (WHO, 2017). Those living in poverty are most vulnerable to these infections which can impair their nutritional status causing diarrhoea, impairment of nutrient intake, digestion and absorption, intestinal inflammation and obstruction, internal bleeding which can lead to loss of iron and anaemia (Welch *et al.,* 2017).

According to WHO (2017) deworming is the best strategy to reduce worm burden and weight and height gain, morbidity. WHO recommend single dose of albendazole (400mg) or mebendazole (500mg) for children aged 12 to 23, preschool children aged 1-4 years of age, and school age children 5-12 years of age living in area where the baseline prevalence of soil transmitted infection is 20% or more among children (WHO, 2017).

This target group for this study is selected, as children under five years constitute the most vulnerable group of a community. Their nutritional status is a sensitive indicator of community health and nutrition. Furthermore, correcting deficiency of micronutrients can help reduce child mortality.

**2. Motivation for the study**

A study by [name] *et al* (2015) in the Vhembe district in Limpopo province indicated that the prevalence of zinc deficiency among children, aged 3 to 5 years, was 42.6% and iron deficiency anaemia was 28%. These data reveal that two micronutrients are significant public health problems in this area of South Africa**.** This proposed study is a continuation from my master’s work. It aims to utilize a food-based approach to address micronutrient deficiencies observed by promoting neglected or underutilized crops such as *Cucurbita Moschata* seeds. In South Africa, *Cucurbita Moschata* is a vegetable grown for its leaves, flesh and flowers. At present the seeds are discarded mainly as a waste (Lewu and Mavengahama, 2010; Dweba and Mearns, 2011) while consuming leaves, flesh and flowers. Yet this practice may be an inadvertent waste of a precious nutritional source of essential nutrients.

These seeds are known to contain numerous vitamins and minerals such as vitamins A and C, zinc, iron, magnesium, and potassium, all of these are needed for resistance against infections (Dweba and Mearns, 2011; Patela and Raufb, 2017). The World Health Organization recommends that the consumption of these seeds may an excellent source of these nutrients (WHO, 2002; WHO/WFP/UNICEF, 2008; http://www.whfoods.com/genpage). Furthermore, Nowfia *et al*. (2012) reported that the seeds could be used as a valuable food supplement.

**2.1. Research Question**

Can the consumption of *Cucurbita moschata* (Butternut) seed paste improve the zinc and iron status of preschool children?

**2.2. Hypothesis**

A null and an alternate hypothesis have been determined.

**Null hypothesis:** Consumption of *Cucurbita moschata* seed paste does not improves zinc and iron status in deficient children.

**Alternative hypothesis:** Consumption of *Cucurbita moschata* seed paste improves zinc and iron status in deficient children.

**2.3. Main aim of the study**

The primary aim of this study is to test the efficacy of consumption of *Cucurbita moschata* (Butternut) seeds in improving zinc and iron status in preschool children in the Vhembe district, Limpopo province of South Africa, and the secondary aim is to describe the nutritional, zinc and iron status of the children. To attain the aims of this study the following objectives have been developed. Objectives of this study are outlined in each phase

**2.5. Expected outcomes**

- Zinc and iron status of the intervention group will improve from baseline levels after consumption of the seeds for 6 months.
- Eating patterns of the participants will improve because of the nutrition education.
- Consumption of fruits and vegetables will increase because of the nutrition education.

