**1.7. *Cucurbita Moschata* (Butternut) seeds.**

*Cucurbita moschata* seeds, also known as butternut seeds are white or brown in colour and are consumed directly by humans as a snack (Karanja *et al*., 2013). Farmers in Africa have cultivated and collected these vegetables and their seeds as an important food source for generations (Aruah *et al*., 2011). According to Cortez-Vega *et al*. (2014), *Cucurbita moschata* is a common seasonal crop that has been used traditionally both as food for humans and animals. In South Africa *Cucurbita Moschata* vegetables are usually grown in the Spring and Summer when there is sufficient rainfall (Shaffer, 2010). Many rural communities have been consuming traditional vegetables and their seeds for centuries. These have contributed immensely to household food security by providing direct access to readily accessible nutrients (Shaffer, 2010; Mpala *et al*., 2013). Currently, *Cucurbita moschata* seeds are discarded as by-products in food processing. Although *Cucurbita moschata* is grown locally in South Africa, the seeds are discarded as waste despite their great nutritional potential. After removing the flesh, in many communities the best seeds are set aside for cultivation the next season.

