***Dietary patterns***

The 24-hour recall will be analysed using the 11-food item to determine dietary diversity score. The FFQ will be analysed using SPSS version 23 for frequencies as daily, weekly, monthly, seasonal or never. Consumption of indigenous foods will be determined using frequencies. Food finder (MRC) will also be used to analyse the nutrient intakes.

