**3.6.3.2. Objectives**:

3.6.3.2.1. To feed the children with the intervention or control for six months

- - - - 1. To assess adherence to the dietary intervention in terms of consuming Cucurbita *moschata* seed paste

**3.6.3.3. Design:** Study design will be a pretest-posttest control group trial, using cluster randomisation, which is a type of scientific experiment, which aims to reduce bias when testing a new treatment (Leedy and Ormrod, 2010). The preschools participating in the trial are randomly allocated either to the group receiving the treatment under investigation or to a group receiving standard treatment (or placebo treatment) as the control (Leedy and Ormrod, 2010). Randomized minimizes selection bias and the different comparison groups allow the researchers to determine any effects of the treatment when compared with the no treatment (control) group, while other variables are kept constant (Leedy and Ormrod, 2010). Randomization will take place at the preschool level. The research will be using single blinded trial with a knowledge of who is receiving the treatment amongst the participants.

- - - 1. **Intervention and data collection:**

The experimental group will receive their normal diet plus paste (grounded *Cucurbita moschata* seeds mixed with cooked *Cucurbita moschata* flesh) and the educational lesson through the song for six (6) months while the control group will receive normal diet plus mashed *Cucurbita moschata* flesh. The participants will consume ½ cup (64 g) (***to be confirmed after development and pilot***) paste (grinded *Cucurbita moschata* seeds mixed with mash *Cucurbita moschata* flesh) twice per week, during lunch with their normal diet while the control will consume mashed *Cucurbita moschata* flesh at the preschool sites over a six (6) month period. Two dishes made from grinded *Cucurbita moschata* seeds mixed with *Cucurbita moschata flesh* will be used to bring variety and improve compliance.

Grounded *Cucurbita moschata seeds* will be packaged at the food science laboratory at the university of Venda before being delivered to preschools. The packaged grounded *Cucurbita moschata seeds will be mixed with cooked Cucurbita moschata flesh at the preschool site. Mashed Cucurbita moschata flesh mixed with grinded seeds and Mashed Cucurbita moschata flesh* will be served to children during their lunchtime under the supervision of the researcher and trained field worker.

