**Table 3.3: Schematic representation of the feeding trial.**

| **Group** |  | **Estimated no** | **Intervention** | **Intervention days (three teams)** | **Quality control** |
| --- | --- | --- | --- | --- | --- |
| Experimental | Preschool 1 | 73 | Normal diet plus seed paste.  Song | Monday  Wednesday | Plate wastage observations and adherence recording |
|  | Preschool 2 | 73 | Normal diet plus seed paste  Song | Tuesday  Thursday | Plate wastage observations and adherence recording |
|  | Preschool 3 | 73 | Normal diet plus seed paste  Song | Monday  Thursday | Plate wastage observations and adherence recording |
|  | Preschool 4 | 73 | Normal diet plus seed paste  Song | Wednesday  Friday | Plate wastage observations and adherence recording |
| Control | Preschool 5 | 73 | Normal diet plus mashed butternut (placebo) | Monday  Wednesday | Plate wastage observations and adherence recording |
|  | Preschool 6 | 73 | Normal diet plus mashed butternut (placebo) | Tuesday  Thursday | Plate wastage observations and adherence recording |
|  | Preschool 7 | 73 | Normal diet plus mashed butternut (placebo) | Monday  Thursday | Plate wastage observations and adherence recording |
|  | Preschool 8 | 73 | Normal diet plus mashed butternut (placebo) | Wednesday  Friday | Plate wastage observations and adherence recording |

The intervention will be implemented over six months or 180 days. On intervention days, Monday to Thursday, the field workers and the researcher will be on site for quality control. They will work in teams of two, one team per preschool. The researcher will change team daily to ensure standardisation and quality control**.**

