3.6.4.2.2. To measure the anthropometry of the study participants (Weight, Height, MUAC)

3.6.4.2.3. Determine the dietary diversity score of participants using 24- hour recall.

3.6.4.2.4. Determine dietary patterns of the study participants using FFQ.

3.6.4.2.5. To determine serum zinc concentrations among pre-school children using flame atomic absorption spectrophotometer before consuming *Cucurbita moschata* seeds.

3.6.4.2.6. To determine the iron status of pre-school children using hemoglobin, serum ferritin, transferrin receptor and C- reactive protein (CRP) before consuming the *Cucurbita moschata* (butternut) seeds.

**3.6.4.3. Design:** The study design will be post trial cross-sectional survey, similar to phase two. Quantitative data will be collected.

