|  | Soya beans |  |  |  |  |  |  |  |  |
|  | Boiled fresh groundnuts |  |  |  |  |  |  |  |  |
|  | Roasted groundnuts |  |  |  |  |  |  |  |  |
|  | Soya mince |  |  |  |  |  |  |  |  |
|  | Processed and packaged peanuts |  |  |  |  |  |  |  |  |
|  | Macadamia nuts |  |  |  |  |  |  |  |  |
|  | Pecan nuts |  |  |  |  |  |  |  |  |
|  | Marula nuts |  |  |  |  |  |  |  |  |
|  | Roasted butternuts seeds |  |  |  |  |  |  |  |  |
|  | Canned Peas |  |  |  |  |  |  |  |  |
|  | Frozen or Fresh cooked peas |  |  |  |  |  |  |  |  |
|  | Dried boiled peas |  |  |  |  |  |  |  |  |
|  | Mungbean (Ndodzi) |  |  |  |  |  |  |  |  |
| **Fruits** | | | | | | | | | |
|  | Apple |  |  |  |  |  |  |  |  |
|  | Banana |  |  |  |  |  |  |  |  |
|  | Orange |  |  |  |  |  |  |  |  |
|  | Avocado |  |  |  |  |  |  |  |  |
|  | Granadilla |  |  |  |  |  |  |  |  |
|  | Lemon |  |  |  |  |  |  |  |  |
|  | Litchi |  |  |  |  |  |  |  |  |
|  | plums |  |  |  |  |  |  |  |  |
|  | Pawpaw |  |  |  |  |  |  |  |  |
|  | Grapes |  |  |  |  |  |  |  |  |
|  | Guava |  |  |  |  |  |  |  |  |
|  | Mango |  |  |  |  |  |  |  |  |
|  | Naartjie |  |  |  |  |  |  |  |  |
|  | Peach |  |  |  |  |  |  |  |  |
|  | Pear |  |  |  |  |  |  |  |  |
|  | Pineapple |  |  |  |  |  |  |  |  |
|  | Sugar cane |  |  |  |  |  |  |  |  |
|  | Apricots |  |  |  |  |  |  |  |  |
|  | Watermelon |  |  |  |  |  |  |  |  |
|  | Mudoro |  |  |  |  |  |  |  |  |
|  | Titshuguru (Natal plum) |  |  |  |  |  |  |  |  |
|  | Titsengele (Sour plum) |  |  |  |  |  |  |  |  |
|  | Mapfilwa |  |  |  |  |  |  |  |  |
|  | Makwakwa (Baboon orange) |  |  |  |  |  |  |  |  |
|  | Masala |  |  |  |  |  |  |  |  |
|  | Baobab fruit |  |  |  |  |  |  |  |  |
|  | Fig |  |  |  |  |  |  |  |  |
|  | Tintoma |  |  |  |  |  |  |  |  |
|  | Nombela (African Litchie) |  |  |  |  |  |  |  |  |
|  | Marula fruit |  |  |  |  |  |  |  |  |
|  | Tinyiyi |  |  |  |  |  |  |  |  |
|  | Xirhomberhombe |  |  |  |  |  |  |  |  |
|  | Mobola plum(muvhula/ timbulwa) |  |  |  |  |  |  |  |  |
| **Vegetables** | | | | | | | | | |
|  | Cooked spinach |  |  |  |  |  |  |  |  |
|  | Stewed spinach (tomato, onion) |  |  |  |  |  |  |  |  |
|  | Stewed spinach (with potato) |  |  |  |  |  |  |  |  |
|  | Stewed spinach with nuts |  |  |  |  |  |  |  |  |
|  | Stewed spinach with milk/cream |  |  |  |  |  |  |  |  |
|  | Boiled Potato skin |  |  |  |  |  |  |  |  |
|  | Shallow fried potato |  |  |  |  |  |  |  |  |

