|  | Baked potato |  |  |  |  |  |  |  |  |
|  | Mashed potato |  |  |  |  |  |  |  |  |
|  | Potato salad with mayonnaise |  |  |  |  |  |  |  |  |
|  | Boiled White-flesh sweet potato |  |  |  |  |  |  |  |  |
|  | Boiled Yellow-flesh sweet potato |  |  |  |  |  |  |  |  |
|  | Boiled Orange-flesh sweet potato |  |  |  |  |  |  |  |  |
|  | Boiled carrots |  |  |  |  |  |  |  |  |
|  | Stewed carrots |  |  |  |  |  |  |  |  |
|  | Raw carrot |  |  |  |  |  |  |  |  |
|  | Carrot salad |  |  |  |  |  |  |  |  |
|  | Boiled pumpkin leaves |  |  |  |  |  |  |  |  |
|  | Boiled Butternut |  |  |  |  |  |  |  |  |
|  | Butternut cooked with margarine and sugar |  |  |  |  |  |  |  |  |
|  | Boiled mushrooms |  |  |  |  |  |  |  |  |
|  | Stewed Baby marrow |  |  |  |  |  |  |  |  |
|  | Boiled Rhanga |  |  |  |  |  |  |  |  |
|  | Tomato gravy with onion |  |  |  |  |  |  |  |  |
|  | Raw Tomato with salt |  |  |  |  |  |  |  |  |
|  | Tomato salad |  |  |  |  |  |  |  |  |
|  | Beetroot salad |  |  |  |  |  |  |  |  |
|  | Canned/bottled beetroot |  |  |  |  |  |  |  |  |
|  | Stewed beetroot leaves |  |  |  |  |  |  |  |  |
|  | Boiled Cabbage |  |  |  |  |  |  |  |  |
|  | Fried cabbage |  |  |  |  |  |  |  |  |
|  | Stewed cabbage (onion, tomato or potato and oil) |  |  |  |  |  |  |  |  |
|  | Cabbage salad |  |  |  |  |  |  |  |  |
|  | Stewed Cowpea leaves with oil, tomato and onion. |  |  |  |  |  |  |  |  |
|  | Stewed Cowpea leaves with peanuts |  |  |  |  |  |  |  |  |
|  | Dried cowpea  leaves with oil, onion and tomato |  |  |  |  |  |  |  |  |
|  | Dried cowpea leaves with crushed peanuts or peanut butter |  |  |  |  |  |  |  |  |
|  | Stewed Pumpkin leaves with flower and baby marrow with groundnuts |  |  |  |  |  |  |  |  |
|  | Stewed Pumpkin leaves with crushed groundnuts |  |  |  |  |  |  |  |  |
|  | Stewed pumpkin leaves with tomato |  |  |  |  |  |  |  |  |
|  | Stewed dried Pumpkin leaves with flower and groundnut s |  |  |  |  |  |  |  |  |
|  | Stewed Muxiji with onion, tomato and salt |  |  |  |  |  |  |  |  |
|  | Stewed Muxiji with crushed groundnuts or peanut butter |  |  |  |  |  |  |  |  |
|  | Stewed Muxiji with Amaranthus and salt |  |  |  |  |  |  |  |  |
|  | Boiled Cleome gynandra with salt (Bangala) |  |  |  |  |  |  |  |  |
|  | Stewed Cleome with tomato, onion and oil |  |  |  |  |  |  |  |  |
|  | Stewed Cleome gynandra with tomato and onion |  |  |  |  |  |  |  |  |

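### Section 2.5 credits a rise in fruit and vegetable intake to the education, but a before-after rise on the FFQ can come from the butternut that the trial serves to both arms

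*Protocol*

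**What the plan says.** - **Outcome.** Protocol section 2.5 lists as an expected outcome: "Consumption of fruits and vegetables will increase because of the nutrition education". The item before it makes the same attribution for eating patterns. Neither names an instrument, a comparator or a threshold.
- **Feeding.** Under Intervention and data collection in section 3.6.3, the experimental children eat a paste of ground seeds and butternut flesh "twice per week, during lunch with their normal diet while the control will consume mashed" flesh, for six months. The schematic of the feeding trial gives the control preschools two feeding days a week on the same day pattern; their entry begins "Normal diet plus mashed butternut (placebo". Only the experimental arm gets the song.
- **FFQ.** After feeding, section 3.6.4.2 repeats the objective: "Determine dietary patterns of the study participants using FFQ". The vegetable part of Appendix D has a row for boiled butternut and another for "Butternut cooked with margarine and sugar". Seeds ("Roasted butternuts seeds") stand under legumes. Nothing tells the respondent to leave out food supplied by the study.
- **FFQ analysis.** The dietary patterns paragraph says: "The FFQ will be analysed using SPSS version 23 for frequencies as daily, weekly, monthly, seasonal or never". No summed fruit and vegetable score is defined.
- **Comparison.** Section 3.6.4.4 plans regression and ANOVA both for change from baseline and for experimental against control.

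**The concern.** The wording in section 2.5 is causal, but what it describes is a rise over time. The first item in that list is explicitly a change from baseline within the intervention group. The chapter plan in section 3.11 mentions a comparison of intervention with control only for zinc and iron status. A before-after reading of the dietary outcomes is therefore the natural one.

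On that reading, the trial's own servings fall into rows that the FFQ counts as vegetables. The English lyrics in section 3.6.1.6 are about butternut and its seeds, so a real effect of the song on vegetables would most plausibly appear in the same rows. Signal and served food could not be told apart.

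Season is a second source of movement. Section 3.12 puts baseline in April 2021 and the post-intervention survey in November 2021, while section 1.7 says that these "vegetables are usually grown in the Spring and Summer when there is sufficient rainfall". The direction of that shift is unknown.

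At stake is a dietary conclusion that credits the education with food the study delivered. The zinc and iron hypothesis is not touched.

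**Working it through.** The plan gives no figure for this outcome, so there is none to reproduce. The check sets the instruments side by side and then sizes the served food.

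**1. Which instrument can show an increase in frequency?**
- The food diary (section 3.6.3.5, Appendix F) covers home food only, but is kept only during the six months of feeding. It has no baseline.
- The 24-hour recall (Appendix C) is taken before and after, but covers one day. It is reduced to an 11-item diversity score, and a nutrient analysis is added. Its prompt asks about food in and outside the home, a household-level note then excludes preschool food, and pumpkin and squash are examples in a scored group. Its treatment of trial food is therefore not clear-cut.
- The FFQ (Appendix D) is the only frequency measure taken at both times. It has butternut rows and no exclusion.

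**2. Size of the served food.** Inputs: 2 servings a week; a portion of 64 g, which section 3.6.3 marks as to be confirmed and which is flesh plus seeds. The flesh share is not stated, so a range is assumed. For scale only, section 1.6 cites 180 g/day of fruit and vegetables at ages 1 to 3, not the trial's 3 to 5.
- Frequency: 2 / 7 = 0.29 servings/day.
- Grams per day = 2 × 64 × flesh share / 7:

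| Flesh share (assumed) | g/day | Share of 180 g/day |
|---|---|---|
| 50% | 2 × 32 / 7 = 9.1 | 5.1% |
| 75% | 2 × 48 / 7 = 13.7 | 7.6% |
| 100% | 2 × 64 / 7 = 18.3 | 10.2% |

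On the form, two servings a week fall in the band for 2 to 4 times a week. A child who previously ate butternut less than weekly could move up to that band on trial food alone.

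**3. Before-after against between-arm.** Let d be the effect of the intervention on other eating, t the seasonal shift, and r the share of trial servings that the respondent reports, all in servings a week.
- Change in the experimental arm = d + t + 2·r(E).
- Change in the control arm = t + 2·r(C).
- Difference = d + 2·[r(E) − r(C)].

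With d = 0 and equal reporting (r assumed):

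| r | Rise from trial food, each arm | Between-arm difference |
|---|---|---|
| 1 | 2 | 0 |
| 0.5 | 1 | 0 |
| 0 | 0 | 0 |

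The rise over time runs from 0 to 2 servings a week with no effect of the song; the difference between arms stays at 0. If the seed-and-flesh paste and the plain mash are reported differently, the cancellation is incomplete: with r(E) = 0.5 and r(C) = 1 (assumed), the difference is 2 × (0.5 − 1) = −1. A gram difference can also remain, because neither the control portion nor the flesh share of the paste is fixed.

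**The case against.** The strongest reply is that section 2.5 is a list of expectations, not an analysis rule. The protocol never says that the FFQ scores this outcome, and scoring detail may stand in an analysis plan that is not shown. The song has its own named test, the two-question quiz in section 3.6.3.6. Section 3.6.4.4 already plans a comparison with a control arm that eats butternut without the song, and there the served flesh and the season largely cancel. All of this stands and limits the point to a before-after reading. It does not remove the causal wording, which is not attached to that comparison, nor the open FFQ rows.

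A reader might infer more than the documents support:
- **That the outcome will be met whatever the song does, or that the FFQ must rise.** A rise is possible, not certain. Parents are named as respondents for the recall, but it is not clear who answers the full FFQ, and a parent may not report preschool lunches. Answers are in bands, and served butternut may replace another vegetable.
- **That a probability of false success can be stated.** It would need a summed score, a standard deviation of change and full reporting, none of which the protocol gives.
- **That trial food also spoils the diet and micronutrient associations in Table 3.5.** There it is genuine intake, and leaving it out would understate exposure.

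**Conclusion.** The point holds in a limited form. A before-after rise on the FFQ, in either arm, cannot be credited to the education, because the instrument does not exclude butternut that both arms are served. The contamination is up to 2 servings a week. In weight it is at most about 18 g/day, assuming that the whole provisional 64 g is flesh and that every serving is reported; it is about 9 g/day if half is flesh, and nil if preschool food goes unreported. Between arms it is about zero servings if reporting is alike. The documents do not support saying that the outcome is bound to be met. The matter is secondary to the zinc and iron aims, but the change is cheap and removes a real ambiguity in attribution.

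**What to change.** 1. **FFQ (Appendix D).** Add one instruction, used at baseline and at six months, that the butternut and butternut-seed rows refer only to food not supplied by the study.
2. **Trial food.** Report it separately from the plate-waste and adherence records. Keep counting it as intake wherever diet is related to zinc and iron status.
3. **Sections 2.5 and 3.6.4.4.** State the fruit and vegetable and eating-pattern outcomes as the experimental-control difference at six months, adjusted for baseline FFQ. Credit any difference to the whole intervention, since the arms differ in both seed paste and song. Do not attribute a simple rise over time to the education.

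The cost is one line on a form and some rewording, with no new visits, staff or measurements. The drawbacks are that the expected increase will be smaller than one that counts trial food, and that parents may not fully separate home from preschool butternut.
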